## Abstract

**Background:**

There are evidence for the efficacy of acupuncture treatment for chronic shoulder pain, however, it remains unclear the best acupuncture modes for effective treatment. We compared the effect of the myofascial trigger point (MTrp) stuck-moving needle acupuncture with that of common acupuncture treatments. Further, we evaluated the efficacy and safety of stuck-moving needle acupuncture for the MTrp in improving pain and range of motions in patients with idiopathic frozen shoulder. The aim of present study is to select an effective therapy for patients with idiopathic frozen shoulder.

**Methods:**

Randomized controlled trial will be conducted in the three clinical centers of Qingyang Traditional Chinese Medicine Hospital, Qingyang Xifeng district People’s Hospital, and Qingyang Second People’s Hospital in China from February 2020 to January 2021. One hundred and eight frozen shoulder patients will be recruited and randomized into one of three groups in a 1:1:1 ratio of the stuck-moving needle acupuncture group, common acupuncture control group, and physical exercise control group. This trial will include a 1-week baseline period, a 3-week treatment period, and a 12-week follow-up period. During the 3 weeks of the treatment period, patients will receive nine sessions of acupuncture. The primary outcome will be related to change in the Visual Analogue Scale (VAS) and measurement of range of joint motion (ROM) from the baseline period to the 12-week follow-up period. Secondary outcome measures will include measurement of pressure pain threshold (PPT), pressure pain tolerance (PTT), Oxford Shoulder Score (OSS), 36-item short form survey, and patient satisfaction evaluation. Adverse events also will be recorded for safety assessment.

**Discussion:**

The results of this trial will allow us to compare the difference in efficacy between stuck-moving needle acupuncture MTrP with that of common acupuncture treatments. The findings from this trial will be published in the peer-reviewed journals.

**Trial registration:**

Acupuncture-Moxibustion Clinical Trial Registry (ChiMCTR1900002862) and Chinese Clinical Trial Registry (ChiCTR1900028452). Registered on 22 December 2019. http://www.chictr.org.cn/showproj.aspx?proj=47354

## Background

### Epidemiology and current management

The shoulder joint is the joint which involves the largest range of human activities. It can perform complicated work and exercise. Therefore, their significance is inevitable in daily work activities of the human being. Shoulder pain is a common disease with high morbidity in patients attending daily outpatient clinics [1–4]. The frozen shoulder is a type of shoulder disease in which the active and passive movements of the shoulder joints are significantly restricted for no apparent reasons. The study carried out by Codman [5] in 1934 pioneered the term “Frozen Shoulder.” Later, the American Academy of Shoulder and Elbow Surgeons defined the disease as “adhesive arthritis of the glenoid-humeral joint” [6]. At present, the two names such as “frozen shoulder” and “adhesive arthritis” are used worldwide. Generally, middle-aged and elderly people in their 40s and 60s are most susceptible to the frozen shoulder disease. In the normal population, occurrence of this disease is about 2 to 5%, whereas diabetic patients are more susceptible to the occurrence rate as high as 20% [7]. The frozen shoulder is mainly divided into idiopathic frozen shoulder and secondary frozen shoulder. Idiopathic frozen shoulder is considered as a diagnosis for all cases in which specific trauma, known comorbidity, or underlying etiology cannot be identified. The clinical characteristics can be defined with shoulder pain and mechanical restriction in all planes of movement of the glenohumeral joint [8]. It is considered to be a self-limiting disease that can resolve within 1 to 3 years. However, shoulder pain and limited mobility in some people may take years and some carry it for life-long [9]. Various studies and researches have shown that 20 to 50% of patients may continue to develop persistent symptoms [10]. The previous studies were carried out with continuous follow-up of 41 frozen shoulder patients for the period of 5–10 years; however, recovery was observed in only 39% of the patients. The long-term pain and limited mobility of most patients seriously affected their normal daily life [11]. It requires a management plan differing from other shoulder conditions [12]. Efforts to find out effective therapies to relieve pain and increase the range of motion are essential to improve the quality life of patients suffering from frozen shoulder.

### Rationale for the use of intervention

Idiopathic frozen shoulder treatment methods are generally divided into three types: operative treatment, conservative management, and minimally invasive treatment [13]. The operative treatment includes arthroscopic capsular release and manipulation under anesthesia, while conservative management includes exercise therapy, superficial heat or cold, electrotherapy, and medication. Minimally invasive treatment includes acupuncture and injections [9, 13]. Recent numerous studies have focused on acupuncture treatments for idiopathic frozen shoulder, as it is safer than medical treatments and has fewer side effects, specifically to remedy for chronic shoulder pains [14, 15]. Based on previous studies, it has been suggested that the strong stimulation of acupuncture may enhance the effects of pain relief by triggering “diffuse noxious inhibitory controls” and may increase the secretion of endorphins by stimulating internal activity of the central nervous system [16, 17]. In addition, acupuncture can inhibit the inflammatory response of the local shoulder joint [18]. However, the acupuncture site, manipulation, and intensity of the stimulation affect the efficacy of acupuncture therapy [19]. The common acupuncture stimulates the acupoints with filiform needles. It is easy to operate and the patient suffers less pain, whereas stuck-moving needle therapy is different from common acupuncture in the needle instrument, manipulation, and stimulation site [20]. Stuck-moving needle applicator applies active motion to the stuck needles fixed at the myofascial trigger points to achieve a benign, suitable, and effective needle volume, eventually to get acupuncture effect. Consequently, stuck-moving needle therapy has higher requirement on the operator and has stronger acupuncture stimulation compared with common acupuncture. The myofascial trigger points (MTrp) have often been used in the treatment of myofascial pain syndrome. Acupuncture is a type of myofascial trigger point therapy which provides immediate relief of pain related with myofascial trigger point [21–23]. Moreover, results from a few studies suggested that the response to trigger points is greater than the response to treating traditional acupoints [24, 25]. These results suggest that the stuck-moving needle stimulation of myofascial trigger points might be effective for patients with idiopathic frozen shoulder. Our pilot study showed that stuck-moving needle was used to acupuncture myofascial trigger point and was effective in improving the pain and movement limitation of the patients with idiopathic frozen shoulder. Physical exercise programs are widely used to resolve the shoulder joint pain which ultimately limits the frozen shoulder, and considered as the effective basic therapy [14] which is also supported by clinical evidences [13]. This information permits the use of physical exercise programs as the basic therapy for a control treatment. The present study was carried out to compare the effectiveness of stuck-moving needle acupuncture Trp and common acupuncture practices.

### Rationale for the trial design

Currently, few studies report on the comparative effectiveness of using stuck-moving needle acupuncture MTrp for idiopathic frozen shoulder. However, clinical studies have reported the benefits of acupuncture [26], but lack the comparison and the effect of different methods. Thus, in this study, we designed a prospective randomized controlled trial to determine the clinical effectiveness of stuck-moving needle acupuncture MTrp and common acupuncture in reducing idiopathic frozen shoulder. Further, we compared them to physical exercise programs. Although the double-blind, placebo-controlled trial is the golden standard to assess a therapeutic effect, however, this method is difficult to use for manipulation technique of sham needling. With a needle stimulation, the process of manipulation for stuck-moving needle acupuncture MTrp and common acupuncture is easily distinguished. Thus, in this study, we have not included blinding and placebo. However, this project uses a blind method for evaluation. Efficacy assessments were performed by third parties, and they were unaware of the grouping situation. In addition to the outcome measurement choice, this study will also evaluate additional patient satisfaction and short form-36 questionnaire (SF-36), and the safety evaluation.

## Method/design

### Study design

The proposed study is a multicenter, prospective, randomized controlled trial that will compare the three currently available treatment options for patients with frozen shoulder. Study will include a 3-week treatment phase followed by a 12-week follow-up phase. Figure 1 shows the trial procedure, and Table 1 illustrates the trial schedule. A total of 108 FS patients will be recruited and randomized into one of three groups in a 1:1:1 ratio of the stuck-moving needle acupuncture group, common acupuncture control group, and physical exercise control group. Patients as a subject will be recruited from 3 clinical centers of Qingyang Traditional Chinese Medicine Hospital, Qingyang Xifeng district People’s Hospital, and Qingyang Second People’s Hospital from February 2020 to January 2021. All patients will be required to provide written consent to participate in the study. The study has been approved by the Ethics Committee of the Qingyang Hospital of Chinese Medicine (No.2019-12-001). Further, we have registered in the Acupuncture-Moxibustion Clinical Trial Registry (ChiMCTR1900002862) and Chinese Clinical Trial Registry (ChiCTR1900028452).

**Fig. 1 Fig1:**
[figure not shown]
Trial procedure

**Table 1 Tab1:**
[figure not shown]
Schedule of enrollment, intervention and assessments for this study protocol

*VAS* Visual Analogue Scale, *ROM* measurement of range of joint motion, *PPT* pressure pain threshold, *PTT* pressure pain tolerance, *OSS* Oxford Shoulder Score, *SF-36* 36-item short form survey

### Participants

#### Participants criteria

The inclusion criteria for patient selection are as follows:
The age shoulder between 40 and 70 years old.Shoulder pain is self-reported, whereas the pain range extends from the medial side of the shoulder to the biceps area or the outside of the deltoid muscle. The VAS score is between 7 and 8 points.The onset of pain lasts for at least 3 months.The stiff shoulder pain is a spontaneous attack, and the shoulder lifting or external rotation function is lost by 50%, and the OSS score is between 50 and 60 points.Being able to actively cooperate with the doctor and sign the consent form to voluntarily receive acupuncture treatment.

#### Exclusion criteria

The exclusion criteria for patient selection are as follows:
The patient has received other treatments that may affect the effect indicators of this study, including oral painkillers for nearly 3 months and physical therapies such as acupuncture and massage.The patient has severe life-threatening primary diseases related to liver and kidney, cardiovascular and cerebrovascular diseases, and mental illness.Patients who are pregnant or breastfeeding which do not meet the inclusion criteria.Exclude other factors related to the diseases such as the history of shoulder trauma within 1 month, shoulder tuberculosis and tumor, rheumatoid arthritis, rheumatic arthritis, gouty arthritis, shoulder subluxation of stroke sequelae, shoulder pain caused by cervical spondylosis, and reflex shoulder pain caused by heart or biliary tract disease.

Note: Patients who meet any of the above criteria will be excluded immediately.

## Recruitment, randomization, allocation concealment, and blinding

### Recruitment

Patients will be recruited via advertisements on hospital website and notice board of clinics.

### Random and allocation of hidden methods

The number of observed subjects will be allocated based on the actual situation of each center. The subjects in each center will be divided into three groups by random number table method and serial numbers will be allocated (such as 1, 2, 3, ..., *N*, this serial number is the ID of the subjects who will participate in the study). Then starting from any number on the random number table, the number of subjects will be selected in the sub-center. SAS (v9.4) software will be used to generate the random numbers corresponding to the above serial number. The number will be divided by 3; if the remainder is 0, then the subject will be included in the acupuncture myofascial trigger points’ group. If the remainder is 1, subject will be included in the common acupuncture group, and if the remainder is 2, then the subject will be included in the functional exercise group. According to the result of the grouping, the random card will be made, sealed in an opaque envelope, and will be kept by a responsible person. In the clinical implementation, the order in which the qualified subjects will be included in the test is in one-to-one correspondence with the sequence number on the envelope, and the envelopes will be opened and grouped according to the prompts on the random card.

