### Sample size estimation

According to the previous researches, the difference between the VAS score before and after treatment in the general acupuncture group was 4.7, with a standard deviation of 1, whereas the difference in VAS score before and after treatment in the functional exercise group was 3.5, with a standard deviation of 1 [14]. In combination with the pilot experimental results from this study, the VAS score before and after treatment of frozen shoulder patients with stuck-moving needle acupuncture dropped by 5.2 and the standard deviation was 1.06. This study was a prospective study with three groups and the sample size as 1:1:1. The sample size was calculated using *F*-test in software SAS 9.4, and we used single-factor analysis of variance to calculate the sample size. The test level was set at *α* = 0.05, β = 0.1, and the test efficiency was set at 1 − *β* = 0.9. The results showed that the test power was 0.931, and the number of samples in each group was not less than 30. By considering the problem of missing samples or losing to follow-up, the sample size will be increased by 20. This means that the minimum sample size of each group will be 36 patients, and finally, the total sample of the three groups will include cases not less than 108.

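### Allocation by remainder after division by 3 gives 1:1:1 only in expectation, so 108 patients do not secure the stated minimum of 36 per group

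*Protocol article*

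**What the plan says.** Three sections of the protocol article bear on this.

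- **Random and allocation of hidden methods.** Lists are made centre by centre: "The subjects in each center will be divided into three groups by random number table method and serial numbers will be allocated". The numbers come from SAS: "SAS (v9.4) software will be used to generate the random numbers corresponding to the above serial number". The arm then follows from the remainder: "The number will be divided by 3; if the remainder is 0, then the subject will be included in the acupuncture" trigger-point group (A). Remainder 1 gives common acupuncture (B) and remainder 2 gives exercise (C). The results go into opaque sealed envelopes, which are opened in sequence. No block, quota, ranking or adjustment step appears. Centre sizes are left open: "The number of observed subjects will be allocated based on the actual situation of each center".
- **Study design.** A total of 108 patients will be "recruited and randomized into one of three groups in a 1:1:1 ratio".
- **Sample size estimation.** The requirement of at least 30 per group is raised for losses, so that "the minimum sample size of each group will be 36 patients" and the three groups together number at least 108.

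**The concern.** The allocation algorithm is spelled out from the random number to the envelope, and nothing in it forces the arms to be equal. Each patient is in effect an independent draw with probability one third per arm. Yet the sample size section treats 36 as a floor for every group, and the study design section sets the total at exactly three times that floor. There is no slack: if one arm has 37, another must have fewer than 36.

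What is at stake is the loss allowance. The six extra patients per group are meant to absorb dropouts. Under this rule, chance imbalance in arm size can use up those six in one arm before anyone has dropped out.

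**Working it through.** **Inputs.** Total N = 108 (study design). Probability 1/3 per arm, independent between patients (remainder rule). 30 per group before losses and 36 after (sample size estimation). Assumed VAS falls of 5.2 in group A (SD 1.06) and 4.7 in group B (same section).

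**Step 1: the plan's own group size.** Reading the stated increase of 20 as 20%, 30 × 1.2 = 36 and 3 × 36 = 108. This reproduces. The power of 0.931 quoted beside the 30 does not follow from the stated means and SDs (a one-way ANOVA gives more than 0.999 at 30 per group), but that is a separate matter and nothing below depends on it.

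**Step 2: chance of meeting the minimum.** With N = 108, all arms reach 36 only at 36/36/36:

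P = 108! / (36!)³ × (1/3)¹⁰⁸ = 0.0076.

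So at least one arm falls below 36 with probability 1 − 0.0076 = 0.992.

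**Step 3: size of the shortfall.**
- One arm's size is binomial(108, 1/3): mean 36, variance 108 × 1/3 × 2/3 = 24, SD 4.9, 95% range 27 to 46.
- P(a given arm is below 30) = 0.0906. Three times this is 0.272. Removing the small overlap where two arms are both below 30, the exact trinomial gives P(at least one arm below 30) = 0.27.
- P(largest minus smallest arm is 10 or more) = 0.50.
- The smallest arm has expected size 31.0 and the largest 41.1.

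**Step 4: effect on precision.** The variance of the A–B difference is proportional to 1/n_A + 1/n_B. To second order, the expected value of 1/n is (1/36) × (1 + 24/36²), and 24/1296 = 1.9%. The exact average over the trinomial also gives a 1.9% rise in variance, about 1.0% in the standard error. For 5.2 against 4.7 at SD 1.06, two-sided t-test power is 0.506 at 36/36 and 0.500 on average under the rule. For the three-group ANOVA at the stated means, an uneven split of 28/36/44 still gives power above 0.999.

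**Step 5: reaching 36 in every arm by recruiting on.** Under the remainder rule this takes about 123 patients on average (95th percentile 142).

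**Step 6: the alternative.** With permuted blocks of 6 stratified by centre, three centres of 36 give exactly 36/36/36. With assumed unequal centres (50/35/23 or 52/33/23), simulated arms ranged from 33 to 38.

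**The case against.** Much of the case on the other side stands.

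- **The rule is valid.** Simple randomisation gives every patient the same chance of each arm, and the next assignment cannot be predicted. That is a merit where patients and acupuncturists know the treatment.
- **Many misses are trivial.** A split of 35/36/37 counts as a failure in the 99.2%. The 27% and 50% describe the practical problem better.
- **1:1:1 is often meant as an allocation probability**, and the remainder rule satisfies that. It does not satisfy a fixed minimum of 36 per group.
- **The sample size section sets 108 as a lower limit**, so recruiting further is not excluded. But the study design section gives 108 as the total, and no rule for continuing is stated.

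Three stronger readings are tempting, and the document does not support them.

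- A reader might infer a skewed allocation of 40:30:30 towards group A, because single digits 0 to 9 leave remainder 0 four times in ten. The section does mention a table ("Then starting from any number on the random number table, the number of subjects will be selected in the sub-center"), but it says that SAS generates the numbers tied to the serial numbers, and single digits are nowhere mentioned. What remains is a wording point: two sources are named where one would do.
- A reader might infer that arm is confounded with centre. The lists are made within each centre with equal probabilities, so imbalance by centre is chance noise, not systematic. No within-centre ratio is promised and centre sizes are not fixed, so there is no stated target to miss. The analysis section also allows covariance analysis where confounding factors affect results.
- A reader might blame the low power of the A–B comparison on this rule. That power is about 0.51 even at 36/36. It comes from the assumed difference and the total size.

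**Conclusion.** The protocol states a group size that its own allocation procedure does not secure. With 108 patients, the minimum of 36 in every group is met with probability 0.8%. In about one trial in four (27%), at least one arm starts below the 30 required before the loss allowance. In half, the largest and smallest arms differ by 10 or more.

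The consequence is limited: no bias, and on average about 1.9% more variance in the A–B difference, or less than one percentage point of power. This should be fixed, since the remedy is cheap, but the trial's validity does not turn on it.

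The figures assume that the remainder rule is applied as written, with independent numbers and equal remainder probabilities, and that recruitment stops at 108.

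**What to change.** For all patients not yet allocated:

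- Replace the remainder rule with a SAS-generated permuted-block list stratified by centre. Let block sizes vary at random (for example 6 and 9) and keep them from recruiting staff. Avoid blocks of 3, whose last assignment is always known once the first two are.
- Name SAS as the only source of numbers and delete the random-number-table wording.
- Keep the sealed, sequentially numbered envelopes.
- Include centre in the analysis model.

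The cost is a short program, new envelopes and a wording change, with no extra patients. The downside is slightly more predictability in a trial whose treatments are open. Exact equality is still not guaranteed: an unfinished block of 9 holds at most 3 of any arm, so arms within a centre can differ by at most 3 among patients on the new list, and those already allocated keep whatever imbalance they have.

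If the remainder rule is kept, state in the study design section that 1:1:1 is an allocation probability, and in the sample size section that 36 is the expected group size, not the minimum.

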### Blind method

This study will use the blind method for evaluation. Efficacy assessments will be performed by third parties who do not know the grouping situation. Further, all participants in the assessment will receive uniform training. Blind statistical analysis will be used in the data summary stage, that is, statistical analysts will be unaware of the grouping situation and content. Randomized staff, study researchers, operators, and statisticians will be kept unaware of the experiment blinded to ensure that subjects, evaluators, and statisticians do not understand the grouping situation.

## Intervention

Participants will be randomly allocated into one of three groups: A, the stuck-moving needling acupuncture MTrp group; B, the common acupuncture group; and C, the physical exercise group as the control group and the basic therapy for groups A and B. Three acupuncturists with at least 5 years of clinical experience in acupuncture practice will be recruited from Chinese Medicine Practitioners, and only these acupuncturists will be allowed to perform all acupuncture sessions. Several training sessions will be carried out prior to the commencement of the study which will ensure consistency in the skills of the acupuncturist. During the 3-week treatment period, patients will receive nine sessions of acupuncture (3 weekly cycles of one treatment every other day, followed by a 1-day break). One-time stuck-moving needles (0.40 mm × 40 mm/0.40 × 25 mm, the patent of Li Zhenquan produced, Beijing, China) and one-time acupuncture sterile needles (0.25 mm × 40 mm/0.25 × 25 mm, Hwato, Suzhou, China) will be used in the trial. All acupuncture treatments will be provided for free to improve adherence to the intervention protocol. Patient and acupuncturist signatures will be required after each acupuncture session to monitor adherence. Other treatments that may affect the effect indicators of this study will be prohibited, including oral painkillers for nearly 3 months and physical therapy such as acupuncture and massage.

